#### Educational control group

Participants in the educational control group will attend two 90-minute educational classes during the 6-month trial period. The classes will taught by experts on topics considered less likely to influence cognition and PA (e.g., nutrition, pain, and oral care).

### Data collection

Assessments will be conducted at baseline and at postintervention (Table 2). Assessment, data entry, and data analysis will be performed by a different researcher blind to group allocation and not involved in delivering the interventions.

**Table 2 Tab2:** List of measurements collected at preintervention and postintervention assessments

Category		Measurement
Primary outcome		National Center for Geriatrics and Gerontology-Functional Assessment Tool (NCGG-FAT)
Secondary outcomes	Neuroimaging	Magnetic resonance imaging (whole-brain and hippocampal volume)
		Geriatric Depression Scale (GDS)
		Quantity of talk (Silmee W20 monitor)
	Physical function	Short Physical Performance Battery (SPPB; balance, side-by-side stand, semitandem, and tandem tests; gait speed; 2.4-m usual pace walk test; and lower extremity strength chair stand test)
		Trail walking test (TWT)
		Handgrip strength
	Physical activity	Triaxial accelerometer (modified GT40-020)
Other outcomes	Self-reported health status interview	International Physical Activity Questionnaire (IPAQ)
		Kihon Checklist (KCL)
		Life-Space Assessment (LSA)
		Pittsburgh Sleep Quality Index (PSQI)
		Short Nutritional Assessment Questionnaire (SNAQ)
		5-Item World Health Organization Well-Being Index (WHO-5)
		Japan Science and Technology Agency Index of Competence (JST-IC)
		Subjective memory complaints (SMCs)
		Hearing Handicap Inventory for the Elderly–Screening Version (HHIE-S)
	Health-related factors	Diseases diagnosed, prescribed medications, blood pressure, smoking status, alcohol intake, living-alone status, outing frequency, falls, fall-related injuries, fear of falling, urinary incontinence, habitual exercise, habitual activity, mobility limitation, hearing aids, vision, walking aids, pain, talking, talking time, outdoor activities, self-efficacy, outdoor social support, self-cognition, quality of life, basic activities of daily living (BADL)
	Body composition and anthropometry	Multifrequency bioelectrical impedance analysis (body fat and muscle volumes)
		Body weight and height

#### Primary outcome

The primary outcome measure is cognitive function at the 6-month postintervention assessment. Cognitive function will be assessed using the NCGG-FAT [19, 20], a multidimensional neurocognitive test, to assess memory (word list memory-I: immediate recognition; word list memory-II: delayed recall), attention and executive function (electronic tablet version of the Trail Making Test A and B), processing speed (electronic tablet version of the Digit Symbol Substitution Test), and visuospatial function (original version of the NCGG-FAT). High test-retest reliability and moderate to high validity were confirmed in community-dwelling older adults for all task components of the NCGG-FAT.

#### Secondary outcomes

Secondary outcomes will be brain and hippocampal volume, mental status, and depressive symptoms, which can potentially explain the mechanisms of the effects of the KENKOJISEICHI activities on the primary outcome. Whole-brain and hippocampal volume will be determined using a 3-T magnetic resonance imaging system (TM Trio; Siemens Healthcare, Erlangen, Germany). Three-dimensional volumetric acquisition of T1-weighted gradient-echo sequences will be performed to produce a gapless series of thin sagittal sections using a magnetization preparation rapid-acquisition gradient-echo sequence (inversion time [TI] 800 milliseconds, repetition time [TR] 1800 milliseconds, echo time [TE] 1.99 milliseconds, and 1.1-mm slice thickness). Axial T2-weighted spin-echo images (TR 4200 milliseconds, TE 89.0 milliseconds, and 5.0-mm slice thickness) and axial fluid-attenuated inversion recovery images (TI 2500 milliseconds, TR 9000 milliseconds, TE 100 milliseconds, and 5-mm slice thickness) will then be obtained for diagnosis.

Depressive symptoms will be measured using the Geriatric Depression Scale [21], which is a self-report screening tool developed to detect depression in older adults. The responses to the 15-item questionnaire will be scored, with scores of 0–4 defined as normal, 5–10 as mildly depressed, and 11–15 as severely depressed [22, 23]. A total score ≥ 5 points is considered to indicate depressive symptoms.

Quantity of talk will be measured using a biosensor device (Silmee™W20; TDK Co., Ltd., Chiba, Japan) for continuous monitoring of the volume of talk. All of the participants will be asked to wear the biosensor over their right wrist for 14 days following their examination while outdoors, except while swimming or bathing, and to maintain their usual activities.

PA will be measured using a triaxial accelerometer (modified HW-100; Kao Co., Ltd., Tokyo, Japan) for continuous monitoring of the intensity of PA. We will calculate parametric values, including the weekly average, for the daily amounts of light-intensity PA (1.5–2.9 metabolic equivalents [METs]) and moderate to vigorous PA (≥ 3.0 METs). The data will be recorded in 4-second epochs for up to 1 day and will be collected using the KAO system installed at the KENKOJISEICHI. The display of the accelerometer will be blinded. For inclusion in the present study, a valid day will be defined as a day in which the accelerometer is worn for ≥ 10 hours, with a total wear duration ≥ 7 days.

Participants in our study will perform three physical function tests. First, the Short Physical Performance Battery is used to measure balance, gait speed, and lower extremity strength [24]. The total score as well as each component score is related to the degree of disability, and these scores are strongly associated with mortality and hospital admission. Second, in the trail walking test, flags are installed randomly at each of 15 positions [25]. Third, handgrip strength will be measured using a handheld dynamometer (T.K.K. 5401 GRIP D; Takei Scientific Instruments, Tokyo, Japan), with participants in a standing position with their arms hanging naturally at their sides [26].

#### Other outcomes

The participants will complete a self-report health status interview to provide information on a variety of health-related factors. PA will be measured using the International Physical Activity Questionnaire [27]. Low, moderate, and high levels of PA will be calculated on the basis of METs for different activities. Basic health will be measured using the Kihon Checklist (KCL) [28]. The KCL consists of 25 items with 6 subscales, including activities of daily living (5 items), physical ability (5 items), nutrition (2 items), oral condition (3 items), seclusion (2 items), forgetfulness (3 items), and mind (5 items). Life-space mobility will be measured with the LSA [29], which is used to obtain a score based on the reported distance traveled during the 4 weeks preceding assessment. Sleep quality will be evaluated using the Pittsburgh Sleep Quality Index [30], which consists of 19 items that produce a global sleep quality score and scores for 7 components (sleep quality, latency, duration, disturbance, habitual sleep efficiency, use of soporific medication, and daytime dysfunction). Simple nutritional evaluation tools will include the Short Nutritional Assessment Questionnaire [31], which contains 15 items for hospitalized patients and has some items that are most useful for outpatient weight loss, loss of appetite, and use of nutritional supplements and/or tube feeding. Mental health will be measured with the Japanese version of the five-item World Health Organization Well-Being Index, which is a short global rating scale used to measure subjective well-being [32]. The respondent is asked to rate how well each of the five statements applies to him or her when considering the last 14 days. Instrumental activities of daily living evaluation tools will include the Japan Science and Technology Agency Index of Competence (JST-IC) [33]. The JST-IC is a modified version of the Tokyo Metropolitan Institute of Gerontology Index of Competence. Cognitive health will be assessed using subjective memory complaints (SMCs) [34]. SMCs combine the Cambridge Mental Disorders of the Elderly Examination questionnaire and the SMC scale. Hearing screening will be conducted using the Hearing Handicap Inventory for the Elderly–Screening Version (HHIE-S) [35]. The HHIE-S is a ten-item questionnaire developed to assess how an individual perceives the social and emotional effects of hearing loss.

#### Health-related factors

Health-related factors that will be assessed through questionnaires will include blood pressure, medical history, medications, education, smoking status, alcohol intake, whether living alone, outing frequency, self-health status, falls, fall-related injuries, fear of falling, urinary incontinence, habitual exercise, mobility limitations, use of a hearing aid, vision, use of a walking aid, pain, talking, talking time, outdoor self-efficacy, and outdoor social support.

#### Body composition and anthropometry

Body composition and anthropometric measurements will include body weight, and fat and muscle volumes will be measured using multifrequency bioelectrical impedance analysis (MC-980A; TANITA Inc., Tokyo, Japan). Height will also be measured.

### Statistical analysis

The data will be double-entered to enable validation. A coauthor, blinded to group allocation, will conduct preplanned statistical analyses for the primary and secondary outcomes. To ensure blinding, he will have no contact with the participants and use random numbers for group allocation. Intention-to-treat analysis will be applied to the outcome variables. Missing data will be imputed with the multiple imputation method [36]. Characteristics will be compared between groups using chi-square tests for categorical variables and the Mann-Whitney U test for continuous variables. Mixed-model analysis of variance will be carried out to test the effects of group, time, and the group × time interaction for all functional fitness tests. p Values < 0.05 will be considered statistically significant. All statistical analyses will be performed using IBM SPSS Statistics version 24.0 software (IBM, Armonk, NY, USA).

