### Sample size

The required sample size for this study was calculated using predictions of 6-month changes in NCGG Functional Assessment Tool (NCGG-FAT) results. On the basis of results of our previous work, we predicted that a change of 2.0 points would indicate a difference [17, 18]. To detect such a difference, with a power of 80% and alpha error of 5%, and considering a 20–30% dropout rate, a sample size of 35 participants per group was required.

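### The stated group-by-time ANOVA does not visibly cover the NCGG-FAT primary outcome, and its valid change-score test is less precise than a baseline-adjusted 6-month comparison

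*Protocol article*

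**What the plan says.** Three parts of the protocol article bear on this.

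- **Statistical analysis.** A blinded coauthor "will conduct preplanned statistical analyses for the primary and secondary outcomes", by intention to treat and with multiple imputation. The only outcome model named follows, a mixed-model ANOVA to "test the effects of group, time, and the group × time interaction for all functional fitness tests". The significance threshold is 0.05. The section does not mention baseline adjustment.
- **Primary outcome.** "The primary outcome measure is cognitive function at the 6-month postintervention assessment", measured with the NCGG-FAT. Table 2 lists the NCGG-FAT as primary and has a separate secondary category for physical function.
- **Sample size.** The number was "calculated using predictions of 6-month changes in NCGG Functional Assessment Tool (NCGG-FAT) results", and "we predicted that a change of 2.0 points would indicate a difference", with 80% power, 5% alpha, 20–30% dropout and 35 per group. No SD or correlation is given.

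The Data collection section gives two assessment times, baseline and postintervention.

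**The concern.** There are two separate problems.

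The first is wording. The model is attached to functional fitness tests, a term the article neither defines nor uses elsewhere. In ordinary usage it suggests physical performance, whereas the primary outcome is cognition. A reader cannot see from the sentence that the NCGG-FAT is analysed with this model.

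The second is efficiency. With two visits, the group × time interaction equals the between-group difference in change. Subtracting the baseline in full is the best use of it only when the correlation between visits is 1. At any lower correlation it adds baseline noise that regression adjustment would remove. In a trial planned at 35 per group before dropout, that precision is worth having, and the baseline measurement is already being collected.

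**Working it through.** **Inputs from the article:** two visits; difference of 2.0 points; 80% power; 5% alpha (taken as two-sided, since this is not stated); 35 per group; 20–30% dropout.

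**Assumptions:** equal variance σ² at both visits; complete data at 6 months; rho from 0.5 to 0.9.

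**The plan's own figure.** The 35 per group cannot be reproduced, because no SD is given. Solving backwards with m completers per arm, SD of change = 2.0 × √(m/2) / (1.960 + 0.842):

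- 20% dropout: m = 35 × 0.80 = 28, so SD = 2 × 3.742 / 2.802 = 2.67
- 30% dropout: m = 35 × 0.70 = 24.5, so SD = 2 × 3.5 / 2.802 = 2.50

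The stated number is therefore consistent with a two-sided test on change if the SD of change lies between about 2.5 and 2.7 points.

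**Variance of the two analyses, per participant:**

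- change score (group × time): 2σ²(1 − rho)
- ANCOVA on baseline: σ²(1 − rho²)
- ratio ANCOVA/change: (1 − rho²) / [2(1 − rho)] = (1 + rho)/2

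**Power.** If the change test has exactly 80% power, its standardised effect is 2.802. ANCOVA divides this by √((1 + rho)/2), so its power is Φ(2.802/√((1 + rho)/2) − 1.960).

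| Assumed rho | Variance ratio | 2.802/√ratio | ANCOVA power | Gain over 80% |
|---|---|---|---|---|
| 0.5 | 0.75 | 3.235 | 89.9% | 10 points |
| 0.7 | 0.85 | 3.039 | 86.0% | 6 points |
| 0.8 | 0.90 | 2.953 | 84.0% | 4 points |
| 0.9 | 0.95 | 2.874 | 82.0% | 2 points |

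Because the change test is fixed at 80%, these figures are the same for 24.5 and 28 completers per arm.

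**Simulation check** (8,000 runs per setting, t-based tests, 28 per arm). Power for change versus ANCOVA was 79.3% vs 88.5% at rho 0.5, 77.8% vs 83.6% at 0.7, and 78.6% vs 79.9% at 0.9. With no true effect, both tests rejected in 4.6% to 5.4% of runs across 25 and 28 per arm. The lost degree of freedom is negligible, and both tests hold their level.

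**The case against.** The strongest reply is that nothing in the stated model is invalid. Under randomisation, the difference in change and the baseline-adjusted 6-month difference have the same expected value. The interaction also matches the change-based sample size, and the section says its analyses cover the primary and secondary outcomes. All of this stands. It also means that a 6-month endpoint alongside a change-based sample size is not a substantive contradiction.

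The size of the gain also cannot be taken from the article. At rho 0.9 it is about 2 points, or about 1 in the simulation. That stands too.

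A reader might go further in three ways that the article does not support.

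- **Inflated false-positive risk.** If either the group or the interaction test could count as success, the risk would be 1 − 0.95² = 9.75%. The article nowhere says that either may count. The figure also includes results favouring control; counting only those favouring the intervention gives 1 − 0.975² ≈ 4.9%.
- **Very low power.** Read as the efficacy test, the group main effect would have about 37%, 22% and 15% power at rho 0.5, 0.7 and 0.8 (28 per arm), because averaging in the baseline visit halves the effect. No section plans that reading. The change-based sample size and the 6-month hypothesis in the Discussion point away from it. Listing the terms of a mixed ANOVA is ordinary description, and a fuller analysis plan may name the confirmatory one.
- **A model only for SPPB, trail walking and grip strength.** Table 2 labels these as physical function. Equating them with the undefined term is an inference.

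**Conclusion.** The point holds as a wording repair plus a free gain in precision; the planned test is not in error. The only named outcome model is attached to an undefined term that does not visibly include the primary outcome. Its interaction test is valid but is less precise than baseline adjustment for every rho below 1, given equal variances at the two visits. From an 80% starting point the gain is about 10, 6, 4 and 2 power points at rho 0.5, 0.7, 0.8 and 0.9. The direction does not depend on the unknown SD, but the size depends on a correlation the article does not report.

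Changing the model does not by itself cure the wording: the text must also name the NCGG-FAT. The Primary outcome section lists several components without designating a single score, and baseline adjustment leaves that open.

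**What to change.** Revise the model sentence in the Statistical analysis section as follows.

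1. Replace the fitness-test term with wording that names the NCGG-FAT score or scores designated as primary, and the continuous secondary outcomes.
2. For each, compare groups at 6 months with the baseline value of the same score as covariate. Use ANCOVA, or a mixed model with a common baseline mean, in all randomised participants with the planned multiple imputation.
3. State that the 6-month group difference, with its 95% CI, is the efficacy test, and that the group and time main effects of a repeated-measures ANOVA will not be used as evidence of efficacy.

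The cost is one degree of freedom and a change of text. No extra data are needed, since baseline is already measured. The article reports the intervention as still in progress, so the change can be made and dated before the allocation is unblinded for analysis.

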## Discussion

Over one billion people, approximately 15% of the world’s population, are estimated to have some form of disability. These rates are increasing because of an expanding aging population and increases in chronic health conditions such as dementia [37]. Cognitive impairment may be associated with disability in older adults [38]. In this study, we will use a randomized controlled trial design to examine the effectiveness of the KENKOJISEICHI daily outdoor behaviors intervention in community-dwelling older adults with MCI. We hypothesize that participants in the KENKOJISEICHI group will maintain significantly higher cognition at the 6-month follow-up than the educational control group. Based on the transtheoretical model of outdoor behavior change, while cognitive training and cognitive exercise can shift people in the preparation and contemplation stages to the action stage, the outdoor behaviors support program is expected to guide participants to the maintenance stage, which is the essential stage for obtaining enduring health benefits from cognition.

Even during the outdoor behavior support period, older participants may return to an inactive lifestyle because of obstacles such as undesirable weather conditions, health issues, and family and community special events. The outdoor behaviors support program is designed to assist group activity, help them reflect upon issues arising, and help the group come up with its own ideas to overcome such issues. In addition to quantitative assessments of mediating social, psychological, and physiological factors, qualitative assessments focusing on self and group habitual activity will clarify how the outdoor behaviors support program will affect maintaining outdoor behaviors in participants’ daily lives.

If the outdoor behaviors support program successfully promotes maintenance of cognition and physical function, this will expand knowledge regarding supporting change in outdoor behaviors among the older population to obtain health benefits related to cognition. Moreover, the effective and less costly outdoor behaviors programs will be useful in creating a more meaningful and sustainable community-based network.

### Trial status

At the time of manuscript submission, we had obtained ethical approval, registered the trial, and successfully recruited participants. The intervention is in progress (Additional file 1).

## Abbreviations

GDS: Geriatric Depression Scale
HHIE-S: Hearing Handicap Inventory for the Elderly–Screening Version
ITT: Intention to treat
JST-IC: Japan Science and Technology Agency Index of Competence
KCL: Kihon Checklist
LSA: Life-Space Assessment
MCI: Mild cognitive impairment
MET: Metabolic equivalents
MRI: Magnetic resonance imaging
NCGG-FAT: National Center for Geriatrics and Gerontology-Functional Assessment Tool
PA: Physical activity
SMC: Subjective memory complaints
SPPB: Short Physical Performance Battery
TE: Echo time
TI: Inversion time
TR: Repetition time
